#### Sample size and allocation

In the first phase of the clinical study, forty participants will be included, and the two eyes will be studied. The participants will be equally distributed into four groups (based on slit lamp/LOCS III classification): participants with incipient, moderate and severe cataracts and participants without cataracts will be included as the control group. The second phase will include at least ten participants, and the two eyes will be studied. Safety will be evaluated for all the recruited participants along the first and second phases.

Since this is a protocol for a pilot study, no sample size estimate was performed. The number of eyes expected to be analysed along the study (i.e. 20 per arm) was considered adequate for this study [30]. The statistical power will be determined at the end of the study for statistically significant results.

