### Statistical analysis

#### Feasibility assessment

The feasibility of the ESUS technique will be evaluated based on cataract detectability, cataract classification and OPE estimative performances and on the ESUS safety.

Cataract detectability will be considered suitable if at least 90% of the cases detected through slit lamp observations are identified by the ESUS.

The cataracts classification will be considered suitable if sensitivity levels higher than 90 %, with a maximum significance level of 5%, are reached.

The system efficacy for the OPE will be considered suitable if the prediction accuracy is higher than 90%.

Since the clinical procedure involved in data acquisition with the ESUS is similar to the used in biometry for IOL power calculation, the procedure viability is not object of the study.

The ESUS safety will be considered suitable under two conditions: (i) there are no occurrence of serious adverse event associated with ESUS whose causes cannot be rectified; (ii) the occurrence rate of mild to moderate ESUS-related adverse events is lower than 5%.

The feasibility study will be considered successful if at least the primary objective, detection of the presence of cataracts, and the secondary objective of cataracts classification (type and severity) are reached and if the safety of the ESUS technique is verified.

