#### OPE estimation

To develop an OPE estimator, the acoustic parameters extracted from the ultrasonic signals in the first phase will be correlated with the maximum energy used in the phacoemulsification surgery for each participant eye. Only surgeries without surgical or postoperative complications will be considered. A confidence interval of 95% followed by multiple comparison correction will be used to assess the significance of the correlations.

In the second phase, the acoustic parameters extracted from the ultrasonic signals will be used to predict the safety and risk intervals of phacoemulsification energy based on the correlation curves. To evaluate the prediction accuracy, surgeons should initiate surgeries at minimum energy levels and increase them gradually until they reach an efficient energy level. Then, the maximum energy level applied during surgery and the occurrence of surgical and/or postoperative complications will be compared with the safe and risk energy intervals predicted with the correlation curves. The system efficacy will be considered suitable if the prediction accuracy is higher than 90%.

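### Power is to be calculated after the study and only for significant results; on the natural reading this restates the p-value and cannot show whether 20 eyes per arm was enough

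*Protocol article*

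**What the plan says.** The section *Sample size and allocation* of the protocol article makes three statements in sequence. First, "Since this is a protocol for a pilot study, no sample size estimate was performed". Second, "The number of eyes expected to be analysed along the study (i.e. 20 per arm) was considered adequate for this study", with a literature reference in support. Third, "The statistical power will be determined at the end of the study for statistically significant results".

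The same section sets the first-phase size: "In the first phase of the clinical study, forty participants will be included, and the two eyes will be studied", divided equally among four groups (three cataract severities and a control group). The second phase adds at least ten participants, again with both eyes.

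Significance is mentioned in two other places. Under *Feasibility assessment*, classification is suitable if sensitivity exceeds 90%, "with a maximum significance level of 5" per cent. Under *OPE estimation*, "A confidence interval of 95% followed by multiple comparison correction will be used to assess the significance of the correlations". Neither section, nor any other in the article, gives a target difference, a standard deviation or an alternative value for a power calculation.

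**The concern.** A pilot may reasonably go without a formal sample size calculation, and that is not the issue here. The issue is what the plan commits to instead.

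The planned calculation has two features that work against it. It is made once the data are known, with no planning effect stated, so the effect seen in the study is the obvious input. It is also made only for results that reached significance, which selects the larger estimates and so the larger power values. The reported figure would tend to look reassuring whatever the true power was.

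What is at stake is interpretation. The sentence directly follows the statement that 20 eyes per arm is adequate, and both the Abstract and the Discussion look ahead to a larger clinical study. A power figure in the results could be taken as confirming the first or as input to the second. Imprecise, non-significant results would have no power figure at all, although they matter as much for planning.

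**Working it through.** **Inputs.** Forty first-phase participants in four equal groups, both eyes (*Sample size and allocation*); 5% level (*Feasibility assessment*). The article does not say whether tests are one- or two-sided; two-sided is assumed unless noted. The effect at which power is evaluated is not stated; the observed effect is assumed in steps 2 to 4 and a fixed effect in step 5.

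**1. The plan's own figure.** 40 / 4 = 10 participants per group, and 10 × 2 = 20 eyes per arm. This agrees with the article. No power figure is stated, so there is none to reproduce.

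**2. Observed power as a function of p.** For a two-sided 5% z-test with observed statistic z:

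observed power = Φ(z − 1.960) + Φ(−z − 1.960)

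The second term is negligible for significant results.

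| Observed p | z | z − 1.960 | Observed power |
|---|---|---|---|
| 0.05 | 1.960 | 0 | 50.0% |
| 0.02 | 2.326 | 0.366 | 64.3% |
| 0.01 | 2.576 | 0.616 | 73.1% |
| 0.001 | 3.291 | 1.331 | 90.8% |

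The sample size does not enter the formula. Recomputing for a two-group comparison with 10, 20 and 40 per arm gave 50.0% at p = 0.05 and 73.1% at p = 0.01 each time.

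**3. Is the floor peculiar to the z-test?** Lowest observed power found for a just-significant result at 5%:

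- t-test, 78 down to 8 degrees of freedom: 50.3% to 52.7%
- four-group ANOVA, 20 or 10 per group: 64% to 69%, depending on group size and how the noncentrality is estimated
- correlation, n = 60 or 30 (the three cataract groups counted as eyes or as participants): 50.1% to 50.2%
- Fisher's exact test, 20 per arm: 53.2%
- one-sided exact binomial, several null values and sample sizes: 55.7% or more

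The exact value varies with the test, but none fell below 50%. If significance is judged at a stricter, multiplicity-corrected level and power is computed at 5%, the floor is higher.

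**4. What selection does.** Simulated z-tests, 20 per arm, 400,000 draws for each standardised effect d (assumed values, eyes treated as independent):

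| d | True power | Mean observed power among significant results |
|---|---|---|
| 0 | 5.0% | 63.8% |
| 0.3 | 15.8% | 68.0% |
| 0.5 | 35.2% | 72.1% |
| 0.8 | 71.7% | 80.1% |

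With no effect at all, the significant results would show average power of 64%.

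**5. The other reading: a fixed effect.** Power then depends only on that effect, the sample size and the level. For the same assumed effects and d = 1.0, a two-group z-test with 20 per arm has power 15.6%, 35.2%, 71.6% and 88.5% at d = 0.3, 0.5, 0.8 and 1.0. With 10 per arm, counting participants, it is 9.9%, 20.0%, 43.2% and 60.9%. (The 15.6% and 15.8% at d = 0.3 differ because this calculation counts one tail and the simulation counts both.) These figures can be computed before the study and are the same whether or not a result turns out significant.

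**The case against.** The strongest objection is that the sentence does not name the effect to be used. The 50% floor and the link to the p-value follow only if power is evaluated at the observed effect. A pre-set alternative, for instance one tied to the 90% thresholds, would break both, and a fuller protocol or analysis plan might specify one. This stands as a limit on certainty: the observed-effect reading is an inference. It does not rescue the sentence, because with a fixed effect there is no reason to restrict power to significant results.

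The second objection is that nothing depends on the figure. This also stands. The criteria for detection, classification, energy prediction and safety do not use power, and the interim analysis section does not mention it. A reader might infer that the sponsor means to justify the sample size retrospectively, or that the next study will be undersized because of this sentence. The article supports neither. Adequacy is asserted in advance from a reference, and nowhere is it said that the larger study will be sized from this pilot's power. Misreading is a possibility, not a stated plan.

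Third, interval methods are often left to an analysis plan, and the section on energy estimation already mentions a 95% confidence interval for the correlations. That is fair, so the absence of such detail is not the complaint. Intervals are proposed because they are the natural replacement for the sentence to be removed.

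**Conclusion.** The sentence is wrong as written, with limited consequences. On the natural reading, the planned power is a restatement of the p-value, is about 50% or more for every significant result, and carries no information on whether 20 eyes per arm was enough. This assumes power at the observed effect, evaluated at a level no stricter than the one used to declare significance; the tabulated percentages are for a two-sided 5% z-test. On the alternative reading the calculation is legitimate, but its restriction to significant results is not. Either way the sentence should change. The feasibility conclusions do not rest on it; the gain is in avoiding a figure that could mislead when the pilot is reported or the larger study is planned.

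**What to change.** Delete the sentence. In its place, state that sensitivity, detection rate, prediction accuracy and correlations will each be reported with a 95% confidence interval whether or not they are significant, using a method that allows for two eyes per participant.

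The interval shows directly what observed power hides. For illustration, suppose 19 of 20 eyes are correctly classified, 20 being the number of eyes from ten second-phase participants. The exact binomial 95% interval is about 75% to 99.9%, against a criterion of 90%. That interval treats the eyes as independent, and positive correlation between a participant's two eyes would widen it. As a sensitivity it also supposes that all 20 eyes have cataract, and the article does not give the second-phase case mix.

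If the sponsor prefers to keep a power statement, it should name a fixed effect, chosen without reference to the results, and apply to every comparison. The cost is one reworded sentence and a choice of interval method; no additional participants or data are needed.

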### Procedures

The participants’ visit schedule is presented in Table 1, and descriptions of the interventions and assessments are given below.

**Table 1 Tab1:** SPIRIT figure showing the schedule of enrolment, interventions and assessments

	Enrolment	Allocation	Post-allocation	Post-allocation			
Time point (day)	t_1_			t_2_	t_3_	t_4_	t_5_
Enrolment							
Demographic and medical record	✓						
Slit lamp and LOCS III	✓						
Inclusion/exclusion criteria	✓						
Informed consent	✓						
Allocation		✓					
Interventions							
Phacoemulsification surgery^b^					✓		
Assessments							
ESUS			✓				
Contrast sensitivity^a^			✓		✓		
Specular microscopy^b^			✓			✓	
Optical coherence tomography^b^			✓			✓	✓
Surgical and postoperative complications record^b,c^					✓	✓	✓
Safety monitoring^d^			✓	✓			
Adverse events			✓	✓	✓	✓	✓

t_1_, diagnosis, recruitment and ESUS procedure; t_2_, safety assessment (a week after t_1_); t_3_, phacoemulsification surgery; t_4_, 1st follow-up (a week after t_3_); and t_5_, 2nd follow-up (a month after t_3_)

^a^Procedure to be performed alternatively on t_1_ or t_3_

^b^Procedures to be conducted only on cataract group

^c^If both eyes received indication for phacoemulsification surgery, data from both surgeries will be collected

^d^A clinical evaluation will be done immediately after the ESUS study and a remote evaluation 1 week later. The procedures will be performed in both eyes

#### ESUS (investigational medical device)

The ESUS components are presented in Fig. 1 and Table 2. The system is composed of an A-scan ophthalmic probe working in pulse-echo mode, with an acoustic working frequency of 20 MHz and focal distance of approximately 8 mm. The active probe surface is shaped to match the cornea curvature, thus favouring their coupling and signal transmission with minimal coupling pressure. The probe front face (that contacts the eye) is manufactured with biocompatible material. The probe is connected to the xScan, whose functions are as follows: send excitation pulses to the probe, generate synchronism signals, digitize the signals captured back by the probe (at a sample frequency of 100 MHz) and preprocess the digitized signals (filtering and amplification). The output of the xScan system is connected to a computer. To establish communication between the xScan and the computer, a programme was developed in C++. This programme is automatically executed through a user-friendly interface (UI) developed in MATLAB (MathWorks, Inc., Natick, MA, USA). The UI was programmed so that the ESUS is automatically configured within safe acoustic outputs.

**Fig. 1 Fig1:**
[figure not shown]
Diagram of the main ESUS components

**Table 2 Tab2:** Manufacturing information of the main ESUS components

Component	Manufacturer	Model
Ophthalmic probe	IMASONIC SAS, Bourgogne-Franché-Comté, France	Custom made^a^
xScan	Tribosonics Ltd., Sheffield, England	Custom made^a^
Computer	ASUSTek Computer Inc., Nieuwegein, Netherlands	VM65N
UI	University of Coimbra	Custom made

^a^Equipment commercialized with a range of customer-defined features

Based on Annex VIII of Regulation (EU) 2017/745 of the European Parliament, the ESUS is classified as a type 2a medical device. This system has been developed in agreement with the Portuguese regulation, Law n° 145/2009 and with Regulation (EU) 2017/745 of the European Parliament.

#### ESUS procedures

i.Participant preparation: To reduce the discomfort generated by coupling the probe, topical anaesthesia (oxybuprocaine hydrochloride) will be applied before starting the acquisitions. However, if the participant has any known contraindication to this anaesthetic, a disposable neutral contact lens will be used as a replacement for the coupling medium between the probe and the cornea.ii.The acquisitions are initiated through a starting button in the user interface, and the probe (previously clean and disinfected) is coupled to the eye after applying eye drops. The probe must be kept in place for a few seconds for automatic signal recording. During this period, signals are visualized in the user interface. Notably, as part of the clinical practice, the participant pupils will be previously dilated.iii.Finally the probe is uncoupled, and the signals are saved in a directory along with other participant information.

#### Demographic and medical record

This information will be obtained from the patient record at the clinical centre with the purpose of confirming the inclusion/exclusion criteria and identifying biases. The data to be recorded are birth date, sex, occupation history, smoking and drinking habits and history of any ophthalmic or systemic diseases and associated treatments.

#### Slit lamp and LOCS III

Slit lamp is a noninvasive method in which cataracts are photographed by retroillumination. The cataract images will be classified according to the LOCS III for cataract type and severity [24]. Cataract classification by this method will be the comparator for this study, used to train the automatic classification system and evaluate its performance in humans.

#### Contrast sensitivity test

This test consists of observing images and identifying shapes of variable contrast. Contrast sensitivity is particularly affected in cataracts. Cases of incipient cataract, where slit lamp observation may not be sufficiently sensitive, may be identified by this method.

#### Specular microscopy

Specular microscopy is a noninvasive technique in which images are reconstructed from the specular reflection of an incident light beam magnified by a microscope. The density and shape of corneal endothelial cells will be evaluated by this method to diagnose corneal endothelial cell loss, which relates to excessive levels of phacoemulsification energy.

#### Optical coherence tomography (OCT)

OCT is a noninvasive diagnostic method, in which the reflection of a low-coherence light beam is used for image reconstruction. OCT will be used for measuring macular thickness to detect the presence of macular oedema, one of the possible postoperative complications of phacoemulsification surgeries [7]. This study is conducted as part of the clinical practice in patients submitted to phacoemulsification surgery.

#### Phacoemulsification surgery

The phacoemulsification procedure will be performed according to normal clinical practice. The maximum energy level used in the phacoemulsification surgery, the phacoemulsification time and possible surgical complications will be recorded to evaluate the appropriateness of phacoemulsification energy levels. This study will not interfere with the clinical surgery protocols.

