## Methods

### Trial design

Pilot, nonblinded and monocentre study.

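### The article says the study leaves surgery unchanged, yet directs how energy is set in phase 2, so maximum energy arises under different conduct when the OPE curves are fitted and when they are tested

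*Protocol article*

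**What the plan says.** Two sections of the protocol article describe how surgery is conducted.

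- Procedures, Phacoemulsification surgery: "The phacoemulsification procedure will be performed according to normal clinical practice". Maximum energy, phacoemulsification time and complications are recorded, and the section closes with "This study will not interfere with the clinical surgery protocols". It makes no distinction between phases.
- Statistical analysis, OPE estimation, phase 2: "To evaluate the prediction accuracy, surgeons should initiate surgeries at minimum energy levels and increase them gradually until they reach an efficient energy level".

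OPE estimation also sets out how the energy data are used. In phase 1 the acoustic parameters "will be correlated with the maximum energy used in the phacoemulsification surgery for each participant eye". The fit is restricted by outcome: "Only surgeries without surgical or postoperative complications will be considered". In phase 2, the maximum energy and any complications are set against the ranges, safe or risky, that the phase 1 curves predict. Efficacy is called suitable if accuracy exceeds 90%.

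Trial design describes a "Pilot, nonblinded and monocentre study". Table 1 places the ESUS acquisition at t1 and surgery at t3. ESUS procedures says the signals are saved.

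**The concern.** The phase 2 instruction is given for the study's own purpose, to evaluate the prediction, and it concerns how the operation is carried out. That is hard to square with a statement that the study leaves the surgical protocols alone. The article does not say that the sequence is already routine at the centre.

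The statistical consequence follows from the contradiction. A curve that relates acoustic parameters to maximum energy also reflects how surgeons came to use that energy. If conduct changes between the fitting phase and the testing phase, disagreement may come from the change rather than from the device, and so may agreement. The accuracy figure would then not show how well the ESUS predicts energy.

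The endpoint also depends on the point at which the surgeon stops raising energy. In a study labelled nonblinded, with no masking of the operating surgeon described, that point needs protection from knowledge of the prediction.

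**Working it through.** **Text comparison**

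| Element | Phase 1 (curves fitted) | Phase 2 (curves tested) |
|---|---|---|
| Recorded variable | Maximum energy, per eye | Maximum energy, plus complications |
| Conduct, Phacoemulsification surgery | Usual practice | Usual practice |
| Conduct, OPE estimation | None described | Directed energy sequence |
| Eyes used | Complication-free only | Complications counted in the comparison |

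The third row contradicts the second for phase 2. The variable has the same name in both phases, but the way it arises differs. The eyes used differ as well; that difference is not quantified here.

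**Possible size**

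The article states no energy SD, no shift between conducts and no form for the predicted interval, so there is no figure to reproduce. What follows is an illustration. Assume normal residuals, a phase 1 interval with 95% coverage, and directed conduct that lowers maximum energy by d residual SDs.

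- Two-sided interval: coverage = Φ(1.96 − d) − Φ(−1.96 − d)
- Upper bound only: coverage = Φ(1.645 + d)

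| d (assumed) | Two-sided | Upper bound only |
|---|---|---|
| 0 | 95.0% | 95.0% |
| 0.5 | 92.1% | 98.4% |
| 1.0 | 83.0% | 99.6% |
| 1.5 | 67.7% | 99.9% |

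For the two-sided interval, a shift of about 0.65 SD is enough to reach the threshold: Φ(1.31) − Φ(−2.61) ≈ 0.905 − 0.005 = 0.90.

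**Chance of meeting the criterion**

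Sample size and allocation gives at least ten phase 2 participants with both eyes studied, so 10 × 2 = 20 eyes if exactly ten enrol and every eye is operated on. Since 18/20 is exactly 90%, exceeding 90% needs 19 or more. With coverage p and eyes treated as independent, the chance is p^20 + 20·p^19·(1 − p):

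- d = 0: 0.74
- d = 0.5: 0.52
- d = 1.0: 0.12
- d = 1.5: 0.004

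These are the two-sided values. With an upper bound only, coverage rises above 95%, so the chance of passing rises above 0.74. The same change in conduct can therefore make the device look worse or better, depending on how a correct prediction is defined.

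**The case against.** The contradiction is hard to dispute. If the directed sequence were already the centre's normal practice, the two sections would agree, but the article does not say so. The objections that carry weight concern how far to go beyond it.

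- **Different quantities.** A reader might infer that the model is trained and tested on different variables. The article records maximum energy in both phases; only the conduct that produces it differs.
- **Surgeon aware of the prediction.** A reader might infer from the nonblinded label, and from acquisition at t1 before surgery at t3, that the surgeon holds the prediction and can steer toward it. The article does not say that the surgeon receives the OPE output, nor that it is computed at t1; only acquisition is placed there. Timelines and methods for outcomes recording says that OPE estimation is implemented in phase 2, without timing it relative to surgery, and the comparison is described after the operation. Such operational detail may stand in the full protocol. What remains is that no masking is described where the endpoint depends on the surgeon's stopping point.
- **Downward bias.** A reader might infer that accuracy must fall. The upper-bound calculation shows that it can rise.
- **Generic magnitude.** The SD, the shift and the interval form are all assumed. The only 95% interval in OPE estimation concerns the significance of the phase 1 correlations. The figures show sensitivity and do not estimate the bias in this trial.
- **Limited consequence.** OPE is a secondary objective, Feasibility assessment does not require it for overall success, and the phase 2 evaluation is described as preliminary.

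**Conclusion.** The point holds in this form: the two sections contradict each other on whether the study directs surgical conduct in phase 2, and they must be reconciled. This review takes no position on which conduct is right. As written, the OPE accuracy criterion tests phase 1 curves on energies that arise under different conduct, and the result may be biased in either direction. The range shown, from 68% to 99.9% coverage for a nominal 95% interval, rests on assumed downward shifts of 0.5 to 1.5 SD, normal residuals and an unstated interval form. The pass probabilities further assume 20 independent operated eyes, although they would come in pairs from ten people.

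The article does not support a claim that surgeons know the prediction, or that accuracy is necessarily understated. The effect falls on a secondary objective with its own success threshold, so the change should be made but does not undermine the overall feasibility decision.

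**What to change.** 1. Reconcile Phacoemulsification surgery with OPE estimation so that the article gives one consistent account of surgical conduct, and so that maximum energy is generated and defined the same way in both phases.
2. If the phases must differ, state that phase 2 tests the curves under different conduct and limit the OPE accuracy conclusion accordingly. The phase 1 curve should not be recalibrated on phase 2 eyes: they are the only eyes described as operated on under the directed sequence, and recalibration would use up the independent test set.
3. State that the phase 2 OPE prediction is computed offline from the saved signals and withheld from the operating surgeon until the surgical record is locked.

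The cost is protocol wording. The signals are already saved at acquisition, so offline prediction needs no extra data collection. The article gives the study status as not yet recruiting, so the changes can be made before any data exist.
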